### Criteria for discontinuing or modifying allocated interventions {11b}

By design, case management is a modifiable form of care, as it is about organizing interventions based on the individuals’ needs, strengths, weaknesses and living situation. As described before, this study is of a pragmatic nature, granting case managers the flexibility to act as they see fit to support participants, while providing the least amount of support necessary, to stimulate self-management.

Complete discontinuation of case management will occur on participants’ request. People with brain injury can continue if their family member wishes to stop. Off note, a form of ‘active discontinuation’ occurs when participants do not need any support at a given moment: case managers will then monitor the participants’ well-being via the ReMinder and will be available when questions or problems do occur, but do not reach out otherwise. Following the intention-to-treat principle, participants who choose to withdraw from case management (i.e. the intervention) will still be asked to participated in the study assessments. Outcomes are no longer collected when participants choose to withdraw from the study (i.e. the assessments).

### Strategies to improve adherence to interventions {11c}

The ReMinder serves as the basis for case managers to monitor if support is needed; participants will receive reminder emails twice a week until they open the ReMinder questionnaire. When two consecutive ReMinder questionnaires (i.e. 3 months apart) are not filled out, participants will be asked by email whether they have trouble getting access to the system, with filling out the questions or whether there is another reason for not using the ReMinder. If they do not respond to any of these emails, their case manager will reach out to explore the reason for this and to determine if further case manager activities are required. Other elements of case management are not subject to adherence as such.

### Relevant concomitant care permitted or prohibited during the trial {11d}

All participants are allowed to receive any form of care that they need. Service use will be measured with a questionnaire. Participants are asked not to participate in any other studies concerning psychosocial or pharmacological care for the duration of this trial.

### Provisions for post-trial care {30}

Depending on the results of the study and available funding, case management will be continued or gradually scaled down. In case of continuation, participants in the control condition will have the opportunity to receive case management after the study period.

### Outcomes {12}

#### Effectiveness

Outcomes measures were chosen according to the aim of case management, which involves the concepts of psychosocial well-being, self-efficacy and (unmet) needs. Assessment will take place at baseline, after 6, 12, 18 and 24 months. The total score of the Hospital Anxiety and Depression Scale (HADS [51];) will serve as the primary outcome measure, other measures (see below) are secondary outcomes.

##### Outcomes for people with ABI

Psychosocial well-being will be assessed using the HADS, the Utrecht Scale for Evaluation of Rehabilitation-Participation (USER-P [49]) restriction subscale and the Life Satisfaction Questionnaire (LiSat [52]). The HADS consists of 14 items scored on a 4-point scale ranging from 0 to 3 with varying anchors. Total scores can be calculated for the full scale (primary outcome). The two subscales (anxiety and depression) will also be computed and analysed as secondary outcomes; subscale scores of > 7 suggest the presence of an anxiety disorder or depression. The psychometric quality of the scale is sufficient [53]. The USER-P restriction subscale consists of 9 items asking about restrictions in vocational, leisure and social activities as a consequence of ABI. Items are rated on a scale from 0 (not possible) to 3 (without difficulty) and a ‘not applicable’ option. The total score ranges from 0 to 100 based on the number of applicable items; higher scores indicate less restrictions in participation. The scale has shown sufficient reliability and validity [49]. The LiSat assesses various aspects of life satisfaction including life as a whole, self-care management, contacts with friends, vocational, family life, partner relationships, financial situation, leisure situations and sex life. The nine items are scored on a ﻿6-point scale ranging from ‘very dissatisfied’ to ‘very satisfied’. The scale has satisfactory reliability and validity [54, 55].

The concept of self-efficacy, one’s confidence in the ability to deal with (health) problems, will be measured as a proxy for self-management, since self-efficacy is a prerequisite for behavioural change. Self-efficacy will be measured with the Patient Activation Measure (PAM [56];), which is a 13-item instrument assessing self-reported knowledge, skills and confidence for self-management of one’s health or chronic condition. Items are scored on a scale of 0 (disagree strongly) to 4 (agree strongly) and a not applicable option. An algorithm is available to transform the scores on the PAM to different levels of self-management, from ‘disengaged and overwhelmed’ to being their own health advocate. The PAM requires a license and sharing of the de-identified data with Insignia Health. The Dutch version of the PAM has shown moderate test-retest ability (*r* = 0.47) [57].

Care needs will be assessed with the Longer-term Unmet Needs after Stroke questionnaire (LUNS [58];). The LUNS consists of 22 items scored with ‘yes’ or ‘no’ and one open ended question on the physical, social, and emotional consequences of stroke. To make the LUNS applicable for people with other types of brain injury, we replaced the word ‘stroke’ by ‘brain injury’ in two items. A validation study of the Dutch version of the LUNS concluded that the scale is reliable and valid [59]. It should be noted that some items merely express worries or a problem rather than needs (e.g., ‘I am worried that I might fall [again] and this is stopping me from doing my usual things’). Nevertheless, we consider the scale to be the most comprehensive scale to assess care needs in the ABI population available in Dutch.

##### Family member outcomes

Psychosocial well-being, self-efficacy and (unmet) needs will also be measured in family members. In addition to the HADS and LiSAT, of which a description is provided above, caregiver burden will be assessed within the concept of psychosocial well-being. The Caregiver Strain Index (CSI [60];) will be used, which consists of 13 items that can be responded to with ‘yes’ or ‘no’ and total scores ranging from 0 to 13; higher scores reflecting higher caregiver burden and substantial burden is indicated by a score of 7 or higher. For people who suffered from stroke, the CSI is the most commonly used scale and recommended in the Dutch stroke care guidelines [61]. The scale has shown sufficient validity and reliability [62].

*S*elf-efficacy will be assessed using the Carer Self-Efficacy Scale (CSES) [63]. The CSES measures self-efficacy with regard to care management and service use, each in 5 items on a 10-point scale from ‘not at all certain’ to ‘very certain’; higher scores on the CSES indicate higher levels of self-efficacy. Reliability and validity of the scale are sufficient [64].

Family members’ needs will be assessed with the Family Needs Questionnaire (FNQ [65]). The scale includes 40 items assessing needs that may arise during acute rehabilitation, soon after discharge and in the long-term after ABI. Subscales include health information, emotional support, instrumental support, professional support, community support network and involvement with care. Family members are asked to indicate the importance of each perceived need and then rate the degree to which the need has been met. The Dutch translation has shown sufficient reliability [66]. Information on the validity of the translation is not yet available, but the English version has shown to be valid [67].

#### Cost-effectiveness and cost-utility

Cost-effectiveness and cost-utility will be determined using the EuroQol (EQ-5D-3L) and a service use questionnaire, included in the assessments on baseline and after 6, 12, 18 and 24 months. The EQ-5D-3L [68] consists of five questions measuring health status. The dimensions covered are mobility, self-care, daily activities, pain or discomfort, and anxiety or depression. These domains are rated as ‘no problem’, ‘moderate problem’ or ‘unable to do’. The EQ-5D-3L has shown good measurement properties [69]. Service use will be measured with a self-report cost questionnaire, which was constructed to collect cost data from a societal perspective. It is based on the steps described by Thorn and colleagues [70] and on the questionnaire used by Rauwenhoff and colleagues [71].

#### Feasibility

The assessment of feasibility is of exploratory nature and will be assessed using the process evaluation framework of Saunders, Evans and Joshi [72]. This involves mapping fidelity (quality), dose delivered (completeness), dose received (exposure), reach (participation rate), recruitment (procedures, maintenance of participant involvement) and context (aspects of the physical, social, and political environment). Data will be collected continuously in the form of registrations by case managers, and focus groups will be held at study end (18–24 months after baseline). Data will primarily be used in a summative and descriptive manner. Quantitative indicators to determine feasibility are:
At least 67% of the participants fills out the ReMinder each wave (every 3 months).Case managers respond to at least 90% of the times patients the request for contact and contact patients 90% of the times this is indicated by the responses in the ReMinder.Satisfaction with case management (beyond monitoring) is rated with a 7 or higher on a scale of 1–10.At least 70% making use of case management (beyond monitoring) would recommend case management to others.

Qualitative indicators are:
Participants and case managers reporting on case management in terms of it being acceptable, feasible and useful.Participants reporting on case manager activities to match their needs (matched care).Participants and case managers reporting on increasing support when necessary and taking steps back when possible (stepped care)Participants reporting on case managers’ expertise and skills, case managers reporting on feeling well-equipped to appropriately support participants’ needs.

#### Other study parameters

The following demographic and injury-related characteristics will be collected at baseline: date of birth, gender, education, date of most recent ABI, type of most recent ABI, date and type of previous ABI(s), hospital admission (yes/no), length of hospital stay of most recent ABI, referral destination at hospital discharge (home or rehabilitation centre).

### Participant timeline {13}

The schedule of enrolment, interventions and assessments can be found in Table 1. All participants will receive the study questionnaires every 6 months until December 2021. Depending on the time of inclusion (up to June 2020), people with ABI will be followed up for 18 to 24 months. A subsample of people with ABI and family members will be approached for additional participation in focus group interviews, taking place at the end of the study (between October and December 2021).The evaluation form will be sent after 1 year and at the final measurement, which can be 18 or 24 months after baseline assessment depending of the time of enrolment.

**Table 1 Tab1:**
[figure not shown]
Schedule of enrolment, interventions and assessments

*The evaluation form will be sent after 1 year and at the final measurement, which can be 18 or 24 months after baseline assessment depending of the time of enrolment

### Sample size {14}

Power calculation was based on the primary outcome measure Hospital Anxiety and Depression Scale (HADS). A study evaluating a monitoring/psycho-educational intervention in patients with possible ABI due to cardiac arrest showed to be effective in improving both anxiety and depressive symptoms with a group difference on the HADS of 3.25 points, corresponding to Cohen’s *d* effect size of 0.36 [73]. With an alpha of .05 and power value of 80%, a sample size of 194 is required to detect such between-group effect in the post-intervention measurement. This number can be adjusted for the correlation between baseline and follow-up data, since baseline measures will be entered in the model as an independent variable, by multiplying the sample size by 1 − *R*^2^ (R is the population correlation between the dependent variable (post-intervention) and the pre-intervention measurement) [74]. *R* is estimated to be at least 0.5, making the sample size 194 × (1 − 0.5^2^) = 146. Taking a drop-out rate of 30% into account, at least 209 people with ABI should be recruited. For each participating person with ABI, the family member who is or would be acting as the informal caregiver will be asked to be enrolled in the study as well. The number of participating family members will not exceed the maximum of 209.

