### Trial design {8}

This is a pragmatic prospective randomized controlled superiority trial with two parallel groups and repeated measures. Randomization will be performed as block randomization with a 1:1 allocation.

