## Statistical methods

### Statistical methods for primary and secondary outcomes {20a}

#### Effectiveness

Multilevel modelling will be used to assess the improvement of case management participants over time compared to care as usual. Primary analysis involves entering time, group and their interaction (exposure) as fixed terms. Separate analyses will be performed to assess 24-month outcomes for the subgroup of participants for whom this data is available. Sensitivity analysis will be performed by extending the resulting models with covariates, controlling for the effects of age, gender and level of education. Covariates will be kept in the model as long as they contribute significantly to the model. Significance of the fixed regression effects will be tested using the appropriate *t*-test (*α* = .05).

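### The base sample size of 194 reproduces only with a one-sided 5% test; under an ordinary two-sided .05 test the stated 80% power is about 70%

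*Protocol article*

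**What the plan says.** All the planning inputs are in the protocol article, under Sample size {14} and Trial design {8}.

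- The target effect comes from an earlier trial in cardiac arrest patients, "with a group difference on the HADS of 3.25 points", given as a Cohen's d "effect size of 0.36".
- The base calculation is: "With an alpha of .05 and power value of 80%, a sample size of 194 is required to detect such between-group effect". It refers to a comparison at the post-intervention measurement.
- That base is multiplied by 1 − R² because baseline enters the model. R "is estimated to be at least 0.5, making the sample size 194" × 0.75, which the article gives as 146.
- A 30% drop-out allowance takes 146 to a recruitment target of 209.
- On design: "This is a pragmatic prospective randomized controlled superiority trial with two parallel groups and repeated measures", and "Randomization will be performed as block randomization with a 1:1 allocation".

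On testing, the Effectiveness part of {20a} says "Significance of the fixed regression effects will be tested using the appropriate" t-test, with alpha = .05. Neither section says whether the test is one- or two-sided, and nothing elsewhere in the article does.

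**The concern.** An alpha of .05 with no qualifier is ordinarily read as two-sided, and calling a trial a superiority trial does not make its test one-sided. On that reading, 194 is too small for an effect size of 0.36 at 80% power. It is exactly the total that a one-sided 5% test requires, which suggests that a one-sided option was used in the calculation and not carried into the text.

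Two things are at stake:

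- **Reading a null result.** The HADS total is the only primary outcome. A non-significant two-sided result would be judged against a claimed 80% power that the calculation does not support. The article's Discussion already warns that a large group of mild cases could mask benefit, so a null result is a real possibility.
- **Calling the primary result.** While sidedness is open, a result with a two-sided p-value between .05 and .10 in the favourable direction counts as significant under one reading and not under the other.

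**Working it through.** **Inputs.** d = 0.36; alpha = .05; power 80%; R = 0.5; drop-out 30% (all from Sample size {14}); 1:1 allocation (Trial design {8}). Sidedness is not stated, so both forms were computed.

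**Step 1: reproduce 194.** The normal approximation per arm is n = 2(z_alpha + z_power)² / d².

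- One-sided: 2(1.645 + 0.842)² / 0.1296 = 95.4, so 96 per arm.
- Two-sided: 2(1.960 + 0.842)² / 0.1296 = 121.1, so 122 per arm.

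The exact calculation (noncentral t) adds about one person per arm:

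| Test at .05 | Exact n per arm | Rounded up | Total |
|---|---|---|---|
| One-sided | 96.09 | 97 | **194** |
| Two-sided | 122.09 | 123 | **246** |

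The stated 194 is matched exactly by the one-sided test. A two-sided test at .10 is equivalent.

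**Step 2: could rounding of d explain it?** For d from 0.355 to 0.365 the exact two-sided total runs from 252 down to 238. For 194 to give 80% two-sided power, d would have to be about 0.404.

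**Step 3: the later steps.** 194 × (1 − 0.5²) = 145.5, so 146. Then 146 / 0.7 = 208.6, so 209. Both are correct, so the question about 194 passes straight through to them.

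**Step 4: power at the planned size.**

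- Before the baseline adjustment, 97 per arm and d = 0.36: one-sided 80.3%, two-sided 70.4%.
- After the adjustment, 73 per arm and d / √(1 − R²) = 0.36 / √0.75 = 0.416: one-sided 80.4%, two-sided 70.4%.

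**Step 5: the same chain, two-sided.** 246 × 0.75 = 184.5, so 185 evaluable. Then 185 / 0.7 = 264.3, so 265 recruited. Against the printed figures that is 39 more evaluable (185 − 146) and 56 more recruited (265 − 209).

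**Step 6: detectable effect at 146 evaluable.** 80% two-sided power is reached at d = 0.404. The implied SD is 3.25 / 0.36 = 9.03 HADS points, so this is 0.404 × 9.03 = 3.65 points, against the planned 3.25.

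**Step 7: sensitivity to R.** Two-sided power with 73 per arm and d = 0.36:

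| R | 0.50 | 0.55 | 0.60 | 0.64 | 0.65 |
|---|---|---|---|---|---|
| Power | 70.4% | 73.5% | 77.1% | 80.3% | 81.1% |

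**The case against.** The arithmetic is not in dispute. The strongest reply is that the article never says the test is two-sided. If a one-sided 5% test was intended, then 194, 146 and 209 are all right, and the fault is an undeclared choice, not a miscalculation. The full protocol, which is not shown, might declare it. This stands in part: the 70% is conditional on a two-sided test. It does not clear the text, because the one fact that would make 194 correct appears in neither section, and readers will supply the ordinary two-sided reading. The 95% intervals in the economic section concern costs and ICERs, so they are not relied on here as evidence about the primary test.

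A second reply is that R is put at 0.5 or more, and that a higher R restores power. It does, but only from about 0.64. The protocol planned on 0.5 and gives no support for 0.64.

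A third is that the planned analysis is a multilevel model over repeated measurements, whose power may differ from that of a single post-intervention comparison. That is true in either direction. The power of the planned model is not established as 70%, nor as 80%. But the article sizes the trial on the single comparison with baseline as covariate and claims no repeated-measures gain. The like-for-like check is therefore the one above.

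Last, the remedy is only wording. That makes it cheap, but the sidedness of the primary test still has to be fixed before the data are seen.

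**Conclusion.** The concern holds. With d = 0.36, alpha .05 and 80% power, 194 is the one-sided figure; the two-sided figure is 246. As written, with no one-sided test declared, the stated 80% power and the totals of 146 and 209 do not follow from their inputs. Two-sided power is 70.4%, a miss probability of about 30% where 20% is claimed.

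This rests on three assumptions: the primary test is two-sided at .05, R equals the planning value of 0.5, and the comparison is the single baseline-adjusted one that the sample size section describes. If a one-sided test was intended, the numbers stand and the defect is that the test is not declared in either section.

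**What to change.** State the sidedness of the primary test in both {14} and {20a}, before the outcome data are analysed, and make the figure match:

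- **If two-sided (the ordinary reading, and the one to keep unless a one-sided test was planned):** keep 209 recruited and 146 evaluable, and replace the power claim with wording such as: at two-sided .05 and R = 0.5, power is about 70% for d = 0.36 (3.25 HADS points), or 80% for d = 0.40 (about 3.65 points).
- **If one-sided:** say so in both sections, give the reason, and report one-sided results consistently.

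The cost is a sentence or two in each section and a less favourable power statement under the two-sided route. No added enrolment is required for this correction. It would be needed only if the sponsor wished to keep 80% two-sided power at d = 0.36, in which case the target would be 265.

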### Recruitment {15}

At each of the three recruiting hospitals, trained hospital staff will select eligible people with ABI from the electronic patient files. The hospital staff explains the aim of the study and the study procedures to the patient and ask whether they have a family member who might be interested in participating as well. When the person with ABI or person with ABI-family-member couple is interested in participation, the hospital staff will send them the study information and notifies the researcher. The researcher will call after a week to clarify any questions patients or family members may have. If they are interested in participating, an appointment will be scheduled with the research assistant to sign informed consent, complete the baseline assessment and perform the randomization. In case the person with ABI is referred to inpatient rehabilitation, the appointment will take place as soon as possible after discharge.

## Assignment of interventions: allocation

### Sequence generation {16a}

Participants (people with ABI or people with ABI-family-member couples) will be randomly allocated with a 1:1 ratio to either the case management group or the care as usual group, using a computerized random schedule, in blocks of six. The randomization block size will not be disclosed to the research assistant who enrols and assess participants, to ensure concealment.

### Concealment mechanism {16b}

The research assistant will be provided with sequentially numbered, opaque sealed envelopes containing randomization information.

### Implementation {16c}

The allocation sequence will be generated by a person who is not involved in the study assessments, using a computerized random number generator (www.random.org/lists/). This person will prepare sequentially numbered opaque envelopes containing the information about the group assignment of the participant and seal and the envelopes. The research assistant, who is blind for the allocation sequence and block size, will enrol participants, open the envelope after baseline assessment is completed and provide participants with the information about treatment allocation.

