## Assignment of interventions: blinding

### Who will be blinded {17a}

At baseline assessment, group allocation will be unknown to both the research assistant and the participants; treatment allocation takes place after completion of the baseline assessment by a research assistant. If people with ABI wish to be visited at home for the follow-up assessments rather than receiving the questionnaires via mail, they will be visited by a member of the research team who is blind to their treatment allocation. Blinding is not possible for the assessment of feasibility.

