#### Effectiveness and cost-effectiveness

The baseline assessment will be completed no more than 2 months after the visit to or discharge from the hospital or, in case of inpatient rehabilitation following hospital discharge, as soon as possible after they leave the rehabilitation centre. Ideally, assessments take place at the participants’ home, but can take place via telephone or questionnaires may be sent and returned by mail in case home visits are not possible (on time). A trained research assistant will explain the study procedures once more and collect the consent form. During home visits, participants fill out the questionnaires on their own and have the opportunity to ask questions. The research assistant will provide support when necessary, for example by reading the questions and possible answers out loud in case of reading difficulties (a common problem after stroke). Information on gender, educational level and living situation will be collected at baseline; date of birth, type and date of most recent and previous brain injuries and discharge destination will be drawn from hospital records by hospital staff. Follow-up measurements will be mailed to the participants, unless people prefer to be assisted, in which case a research assistant (blind to treatment allocation) will visit them at home.

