#### Project team

Principal (CvH) and coordinating (APMS; CR interim) investigators, overall project leader (JZ), intervention project leader (NJ), ReMinder monitoring tool project leader (KJ, MD)
Agreement of final protocol;Recruiting hospital staff and assistance with recruiting procedures;Implementing ReMinder;Entering participants in case management group into monitoring tool;Recruitment, training and supervising case managers;Collecting registrations of case management activities;Organizing project team meetings.

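### Allocation concealment is weaker than it need be: one fixed block size of six, with the envelope opened by the research assistant who takes consent and runs baseline

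*Protocol article*

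**What the plan says.** Under Sequence generation {16a}, participants are "randomly allocated with a 1:1 ratio", "using a computerized random schedule, in blocks of six". No variation in block size is stated. The safeguard is in the same section: "The randomization block size will not be disclosed to the research assistant who enrols and assess participants, to ensure concealment".

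Under Concealment mechanism {16b}, the research assistant holds "sequentially numbered, opaque sealed envelopes containing randomization information". Under Recruitment {15}, one appointment with the research assistant covers consent, baseline and randomisation. Under Implementation {16c}, the assistant enrols the participant and is then to "open the envelope after baseline assessment is completed and provide participants with the information about treatment allocation".

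For follow-up, questionnaires go by post unless the participant prefers help. On those who want a visit, Who will be blinded {17a} says "they will be visited by a member of the research team who is blind to their treatment allocation". The data-collection section (Effectiveness and cost-effectiveness, under {18a}) says "a research assistant (blind to treatment allocation) will visit them at home".

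**The concern.** Concealment requires that whoever enrols the next participant cannot anticipate the arm. Here the enrolling person also learns each allocation as the envelope is opened, and the list balances exactly after every six envelopes. Someone who follows the sequence can know some coming allocations with certainty and guess others better than by chance.

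Two things could be affected. The first is who enters which arm. Baseline may fall up to 2 months after the hospital visit or discharge, so the order of enrolment visits has some slack, and the assistant conducts the consent conversation. The second is the baseline questionnaire where the assistant helps, for example by reading items aloud. The primary outcome, the HADS total, is self-reported in an open trial, and the sample size section relies on its baseline value as a covariate.

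A smaller matter follows from the same step. The assistant who announces an arm is unblinded for that participant, and assisted follow-up visits are also assigned to a research assistant.

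**Working it through.** **Inputs.** Block size 6 and ratio 1:1 (Sequence generation {16a}), so m = 3 per arm in each block. Recruitment target 209 (Sample size {14}), used only for scale. The article gives no predictability figure, so there is nothing of its own to reproduce.

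**Can the block size be inferred?** With this list the arm counts are equal at envelopes 6, 12, 18 and so on, without exception. Under unrestricted 1:1 randomisation, six allocations split 3:3 with probability C(6,3)/2^6 = 20/64 = 31.25%. Five exact splits in a row would have probability 0.3125^5 = 0.3%. The target of 209 contains 34 complete blocks (209/6 = 34.8), so the pattern would be visible early to anyone who kept a tally.

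**Allocations fully determined.** Once one arm has used its three places, the rest of the block is forced. Over the 20 possible blocks, 1, 2 or 3 places are forced with probability 60%, 30% and 10%:

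- mean = 1 × 0.6 + 2 × 0.3 + 3 × 0.1 = 1.5 per block, which agrees with 2m/(m + 1) = 6/4 = 1.5
- share = 1.5/6 = 25%; 0.25 × 209 ≈ 52 participants

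**Best guess.** The observer always guesses the arm with more places left and tosses a coin when they are equal:

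- expected correct = m + ½ × (2^6/C(6,3) − 1) = 3 + ½ × (3.2 − 1) = 4.1 per block
- share = 4.1/6 = 68.3%; 0.683 × 209 ≈ 143, against 0.5 × 209 ≈ 104 by chance

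**How much each remedy could do.** The same enumeration for other fixed sizes, each known to the observer:

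| Block size | Fully determined | Best guess right |
|---|---|---|
| 4 | 33% | 71% |
| 6 | 25% | 68% |
| 8 | 20% | 67% |
| Enroller sees no earlier allocations | 0% | 50% |

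A larger fixed block gains little. Removing the enroller's view of past allocations gains most, and varying the block size makes the remaining pattern harder to infer.

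**When the limits apply.** The figures hold for one person who sees all envelopes and has inferred the block size. The section on the coordinating centre {5d} speaks of research assistants in the plural, gives no number, and does not describe how envelopes are divided. If several assistants draw in turn from one list without sharing what they saw, predictability is lower. If each held whole consecutive blocks (an assumption), it would be the same.

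**The case against.** The case for the plan is substantial, and most of it stands.

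- Envelopes are opaque, sealed and opened only after baseline, so the current participant's arm is not seen beforehand. What the enroller can hold is a better guess.
- A reader might infer that the assistant chooses who is approached. Hospital staff select patients from the files and explain the study, and a researcher telephones a week later. The assistant enters at the enrolment appointment, and no section says that the assistant sets its date. The room for selection is therefore narrow.
- A reader might also infer that one person opens the whole list. The singular in Implementation {16c} does not establish this.
- Participants complete the baseline questionnaires themselves, unaware of their arm, with help only when needed.
- The tempting stronger reading is that the follow-up blind is lost for everyone an assistant enrolled. The text does not support it. Both follow-up statements require a visitor blind to that participant's allocation, and this excludes whoever opened the envelope. With several assistants, another can go. Nor is the project team named as follow-up visitors, so its knowledge of allocations through the monitoring tool does not breach that blind.
- How visits are shared out may be set down in the full protocol, which an article condenses.

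These points limit the size of the concern but leave its core: one fixed block size, and one role that both learns past allocations and carries out later enrolments.

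**Conclusion.** The point holds as a weakness of concealment that is cheap to reduce, not as a failure of concealment or blinding. At most, on average, 25% of allocations are fully determined and 68% can be guessed correctly, if one person sees all envelopes and infers the block size. With several assistants drawing on one list the figures are lower, by an amount that cannot be computed because their number is not given. These figures measure the opportunity to predict. They are not an estimate of bias in the HADS, and nothing in the article allows one.

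On follow-up the finding is narrow. The blind is required, but the same role is named for enrolment and for assisted visits, and the article does not say outright that they must be different people. It concerns only assisted visits, since questionnaires are posted by default.

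**What to change.** 1. For any remaining enrolment, generate the sequence with randomly varying block sizes.
2. Move the opening of the envelope and the notice of allocation to an existing team member who is already unblinded and does no assessments. The project team's tasks include "Entering participants in case management group into monitoring tool", so such a person exists. The assistant confirms that baseline is complete; that member then opens the next envelope and tells the participant. The assistant is not told the arm.
3. State in {17a} and {18a} that the assistant who opened or announced an allocation does not make that participant's assisted follow-up visits. This puts the existing blinding requirement into a rule that can be checked.

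**Cost.** Participants learn their arm slightly later, one task moves between existing staff, and the rest of the list is regenerated. No added staff or participants are needed. The member who opens envelopes will know the run of allocations, so that person should also stay out of decisions on enrolment.

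**Timing.** Items 1 and 2 help only while inclusion is open. The Trial status section expected it to close in September 2020 and the article is dated November 2020, so little or nothing may remain. Item 3 stays useful throughout follow-up, which runs to December 2021.
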